### Secondary outcomes

Secondary outcome measures will be differences in the extent of lung inflammation dissipation on US images, pulmonary function, blood gas analysis, fingertip arterial oxygen saturation (SaO_2_) monitoring, serum inflammatory factor levels, the sputum excretion volume, time to the disappearance of pulmonary rales, pneumonia status score, and course of pneumonia.

#### Lung ultrasound scoring system

US will be performed before and 7 days after treatment by sonographers with certified competency in thoracic US, blind to CT findings. Chest scans are performed using the convex 3.5–5 MHz and linear 4–8 MHz probes of the US equipment, with the patient in the sitting position. According to previous studies [18], each hemithorax was divided into 4 regions: anterior-lateral sector, posterior sector, upper halve of the third intercostal space, and lower half of the third intercostal space. The evaluation criteria for pulmonary severity classification will be based on the scoring system proposed by Soldati et al. [19] (0 = regular pleural line, A-lines present; 1 = indented pleural line, focal B lines; 2 = broken pleural line, subpleural consolidations; and 3 = white lung with or without consolidations).

#### Pulmonary function

Pulmonary function tester will detect vital capacity (VC), forced vital capacity (FVC), forced expiratory volume in one second (FEV_1_), peak expiratory flow (PEF), and maximal mid-expiratory flow (MMEF) before and 7 days after treatment.

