#### Secondary objectives

To determine whether there is a difference in pulmonary function between LIPUS treatment group and control groupTo determine whether there is a difference in arterial oxygen saturation and serum inflammatory factor levels between LIPUS treatment group and control groupTo determine whether there is a difference in the improvement of clinical symptoms among patients

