### Eligibility criteria {10}

Eligible participants will undergo laboratory and imaging examinations to confirm the diagnosis of viral pneumonia and to assess eligibility to participate in the study.

Patients who meet all the following enrollment criteria will enter this study after signing the informed consent: (1) age 18–80 years old; (2) hospitalized patients had pneumonia-related symptoms, computed tomography (CT) examination met the diagnostic criteria of pneumonia, and the etiology examination suggested a viral origin; (3) patients who can cooperate with various examinations during clinical research; (4) the patient participates voluntarily, and he/she or his/her family agrees and signs the informed consent.

Patients who meet the following criteria will be excluded: (1) other types of pneumonia, such as bacterial pneumonia, mycoplasma pneumonia, falling accumulation pneumonia, etc.; (2) patients with bronchiectasis or lung malignancies; (3) patients with chest skin injury who cannot wear the LIPUS device; (4) pregnant and breastfeeding women; (5) contraindications to the therapeutic ultrasonography (US), including dermatological conditions, local abnormal sensations in the chest or back, epilepsy, etc.; (6) patients with mental illness or unable to communicate normally with staff.

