## Statistical methods

### Statistical methods for primary and secondary outcomes {20a}

Analysis of baseline characteristics of the three groups will be summarized by appropriate descriptive statistics. Analysis of both the primary and secondary outcomes will be performed blinded to treatment assignment and analyzed on the intention-to-treat approach [22], with all randomized participants retaining their original randomization group. If these missing data are judged to be random, multiple imputations of the chained equation will be used to address missing data caused by lost access and non-response.

Normally distributed data were expressed as the mean (standard deviation), whereas data not normally distributed was expressed as the median (interquartile range). The independent sample test was used for the comparison between groups, and the paired sample test was used for the comparison within the group before and after treatment. For clinical symptoms, variables were expressed as percentages. A *χ*^2^ test or Fisher’s exact test was used to compare categorical data. The conventional level of 0.05 for statistical significance was adopted to evaluate the *p*-values. Statistical analysis was carried out by using SPSS software, version 26.

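### The stated between-group test for spirometry makes no use of the pre-treatment reading, which costs power with about 22 patients per arm

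*Protocol article*

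**What the plan says.** The protocol article, Secondary objectives, lists first: "To determine whether there is a difference in pulmonary function between LIPUS treatment group and control" group. The Pulmonary function section describes the measurement: "Pulmonary function tester will detect vital capacity (VC), forced vital capacity (FVC), forced expiratory volume in one second", followed by peak flow and "maximal mid-expiratory flow (MMEF) before and 7 days after treatment". Each patient therefore has a reading at both time points. No percent-predicted value, z-score or reference equation is named.

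The Secondary outcomes section defines the endpoint only loosely: "Secondary outcome measures will be differences in the extent of lung inflammation dissipation on US images, pulmonary function, blood gas analysis" and so on. It does not say whether the day-7 value or the change is meant.

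Eligibility covers "age 18–80 years old". There is no sex criterion apart from the exclusion of "pregnant and breastfeeding women".

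The statistical methods section {20a} gives the analysis: "The independent sample test was used for the comparison between groups, and the paired sample test was used for the comparison within the group" across time. It names no covariate, and the allocation section states no stratification.

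**The concern.** VC, FVC, FEV1, PEF and MMEF are absolute volumes and flows. In adults of both sexes over a 62-year age span, part of the spread between patients reflects who they are and not how their pneumonia is resolving. A two-sample test on day-7 values leaves all of that spread in the error term. The plan already collects the reading that would remove much of it, but it uses that reading only for a before-after test inside each arm, which does not answer the LIPUS-versus-control question.

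Elsewhere the protocol does relate outcomes to the patient's own starting point. The CT absorption rates are percentages of the baseline lesion, and the PSI response is a drop in risk level. Spirometry has no such form. At stake is a listed secondary objective that could end in an uninformative null result from small arms.

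**Working it through.** **Inputs from the protocol.** Sample size section: 66 participants at 1:1:1, so 66/3 = 22 per arm; two-sided α = 0.05. The plan's inflation for dropout reproduces: 66/0.95 = 69.5, rounded up to 70. The 66 itself cannot be reproduced, because no effect size or standard deviation is given. The Abstract's figure of 60 would mean 20 per arm and somewhat lower power throughout.

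**Inputs assumed, because the documents give none.** FVC standard deviation (SD) 1.0 L at both time points, with 0.8 and 1.2 L as a range; true LIPUS-control difference 0.5 L, with 0.3 L as a smaller case; correlation r between the pre-treatment and day-7 readings from 0.5 to 0.9.

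**Formulas.** Power is that of a two-sided two-sample t-test (noncentral t, 42 degrees of freedom; one fewer for ANCOVA changes nothing at this rounding). The noncentrality is (difference/SD_eff) × √(22/2), where SD_eff is:
- day-7 value, unadjusted: SD
- change from baseline: SD × √(2(1 − r))
- ANCOVA on baseline: SD × √(1 − r²)

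**Results for SD 1.0 L and a true difference of 0.5 L:**

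| r | Day-7 value, unadjusted | Change, unadjusted | ANCOVA on baseline (SD_eff) |
|---|---|---|---|
| 0.5 | 37% | 37% | 46% (0.866) |
| 0.7 | 37% | 55% | 62% (0.714) |
| 0.8 | 37% | 73% | 77% (0.600) |
| 0.9 | 37% | 95% | 96% (0.436) |

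The difference detectable with 80% power is 0.86 L unadjusted. With ANCOVA it is 0.86 × SD_eff, about 0.75, 0.62, 0.52 and 0.38 L for the four correlations.

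**Sensitivity.** With SD 0.8 or 1.2 L, unadjusted power for 0.5 L is 53% or 27%; with ANCOVA at r = 0.7 it is 81% or 47%. For a true difference of 0.3 L at SD 1.0 L, power is 16% unadjusted and 20%, 28%, 37% or 61% with ANCOVA at the four correlations. A normal approximation gives values zero to two percentage points higher.

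**Normalisation without baseline, for comparison.** If age, sex and height explained 40% to 70% of the variance and were removed, SD_eff would be SD × √(1 − R²). Power for 0.5 L would be 55% to 84%, and the difference detectable with 80% power 0.67 to 0.47 L. This gain overlaps with the baseline gain, and the two should not be added.

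**The case against.** The strongest objection is that the Pulmonary function section describes a measurement and does not define an endpoint. A reader might infer that the plan commits itself to comparing raw litres at day 7. No section says so, and none rules out percent predicted or change; the reporting scale may sit in a fuller document. That stands, so the finding is conditional on day-7 values being compared. What is not silence is the test: the article does state its between-group method, and that method has no covariate. Applied to changes instead, it would still have lower power than ANCOVA at each correlation considered, although at r = 0.9 the gap is negligible.

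A reader might also infer that age, sex and size would swamp any LIPUS effect. The documents give no SD or effect on which to base that. On the assumptions above, adjusting for baseline in litres alone recovers much of the loss once r is about 0.7 or more.

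Finally, a reader might infer that a chance excess of men in one arm could produce a spurious result. If half the patients are men, two arms of 22 differ by five or more men with probability about 17%. That is not a false-positive rate. Under randomisation the spread due to age and sex is already in the test's standard error, so such imbalances are covered by the nominal 5%.

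It is also fair to say that being listed first gives spirometry no formal rank among the secondary outcomes, and that 22 per arm is too few for small effects under most of these choices.

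**Conclusion.** The point holds as a matter of precision. The stated between-group test ignores a baseline reading that the trial already collects, in a population where stable differences between patients are likely to be wide. On assumed values (SD 1.0 L, true FVC difference 0.5 L, 22 per arm), power is about 37% on unadjusted day-7 values, against about 46% to 96% with baseline adjustment for r from 0.5 to 0.9. The size of the gain depends chiefly on r. That is uncertain in acutely ill patients recovering over a week, and at r = 0.5 the gain is modest. The documents do not support a claim of bias, of an inflated error rate, or of a declared intention to compare raw litres. Since this is one of several secondary outcomes, it is a change that should be made and not a threat to the trial's main conclusion.

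**What to change.** In the statistical methods section {20a}, state that LIPUS and control are compared on the day-7 value of each spirometry variable by ANCOVA, with the patient's own pre-treatment value of the same variable as covariate. Preferably express both values as percent predicted or z-score for age, sex and height, since the same relative recovery is a larger absolute change in a larger person. Report the raw volumes and flows descriptively.

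The cost is one sentence in the protocol or SAP. No extra test or visit is needed, because spirometry is already done at both times. The predicted scale also requires height to be recorded and a reference equation to be named. If that is unwanted, baseline-adjusted raw values would still capture the gain shown in the ANCOVA column.

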#### Blood gas analysis and fingertip SaO_2_ monitoring

The blood gas analyzer will detect the arterial blood partial pressure of oxygen (PaO_2_), arterial blood carbon dioxide partial pressure (PaCO_2_), SaO_2_, and the pH value before and 7 days after treatment. The fingertip photoelectric sensor will also be used to measure the SaO_2_, and the nursing staff will record the data before treatment, 2 h after daily treatment, and after the total course of treatment.

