#### The sputum excretion volume

For patients who can cough spontaneously, nurses will collect and record the amount of sputum that can be excreted in 24 h, and those with negative pressure suction will use a disposable sputum suction device to record the amount of sputum excreted after each treatment. Collection by trained nurses takes place daily at 8:00 am and ends at 8:00 am the next day. Less than 10 ml/24 h is a small amount of sputum, 10–150 ml/24 h is a moderate amount of sputum, and more than 150 ml/24 h is a large amount of sputum. The color and consistency of the sputum will also be recorded.

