## Discussion

The pathological mechanism of viral pneumonia mainly involves a series of “cytokine storms,” tissue edema, vascular endothelial damage, increased vascular permeability, and thrombosis, which leads to a series of clinical symptoms, and may occur dyspnea or impaired oxygenation in severe cases [23, 24]. At present, the focus of treatment for diagnosed patients is symptomatic and we try to use the mechanical and biological effects of LIPUS for treatment.

On the one hand, specific ultrasound intensity, frequency, pulse width, and duration are used for non-invasive physical therapy, and on the other hand, the anti-inflammatory, anti-thrombotic, and pro-reparative effects of LIPUS are combined to relieve the lung condition and reduce the clinical symptoms of patients. Mitogen-activated protein kinase (MAPK) and nuclear factor-kappa B (NF-κB) are classical inflammatory response pathways. A large number of studies have found that the above inflammatory pathways are significantly inhibited after LIPUS irradiation and inflammatory cytokines such as TNF-α, IL-1β, and IL-6 decreased accordingly [25, 26]. The potential of LIPUS to regulate the phenotype of inflammatory cells and reduce the number of neutrophils and inflammatory macrophages was also observed in the musculoskeletal injury model [27, 28].

In this study, we randomly divided patients with viral pneumonia into three groups and evaluated the efficacy of LIPUS by comparing the pulmonary inflammatory state after treatment with the control group and the self-control group. In addition to the control group, we also set up a self-control group to better eliminate the impact of individual differences on the results. If the research results suggest that the curative effect of the LIPUS treatment group is significantly better than that of the control group and the self-control group, it indicates that the LIPUS treatment is effective; if the curative effect of the LIPUS group is better than that of the control group, but there is no difference with the self-control group, it indicates that the LIPUS intervention effect is fair. The statistical difference may be due to individual differences, and the sample size needs to be further expanded for evaluation; if the curative effect of the LIPUS group is not statistically different from that of the control group and the self-control group, LIPUS therapy can be considered poor.

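### Oxygenation outcomes are raw PaO2 and SaO2 with no record of inspired oxygen, so oxygen given by need can attenuate or mask a real LIPUS effect on them

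*Protocol article*

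**What the plan says.** Under Blood gas analysis and fingertip SaO2 monitoring, the article begins: "The blood gas analyzer will detect the arterial blood partial pressure of oxygen (PaO_2". The full list of analyser variables, taken before and 7 days after treatment, is "arterial blood partial pressure of oxygen (PaO_2_), arterial blood carbon dioxide partial pressure (PaCO_2_), SaO_2_, and the pH value". The section continues: "The fingertip photoelectric sensor will also be used to measure the SaO_2", and on timing, "the nursing staff will record the data before treatment, 2 h after daily treatment, and after the total course of treatment". Inspired oxygen fraction, oxygen flow, delivery device, a room-air condition and PaO2/FiO2 appear nowhere in the article.

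The Secondary objectives include the difference in arterial oxygen saturation between the LIPUS and control groups. Statistical methods {20a} gives the analysis: "The independent sample test was used for the comparison between groups". It names no adjustment for oxygen support.

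On the population, Eligibility criteria {10} requires that "hospitalized patients had pneumonia-related symptoms". It sets no upper limit on severity and does not exclude patients on oxygen. The Discussion says that patients "may occur dyspnea or impaired oxygenation in severe cases", and the sputum section plans for "those with negative pressure suction will use a disposable sputum suction device". The concomitant-care section {11d} names nutritional support and is silent on oxygen.

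**The concern.** PaO2 and saturation reflect both how well the lung works and how much oxygen is being breathed. In hospital the second is adjusted in response to the first: patients with low readings receive oxygen, and those who improve are weaned. A raw value taken without its inspired oxygen can therefore rank a sicker patient above a healthier one, and a patient who improves enough to come off oxygen can show a lower reading than before.

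If LIPUS works, fewer LIPUS patients than controls should need oxygen. The readings of the worse-off controls are then lifted more often, and the raw means of the two arms move together. What is at stake is a named secondary objective and the blood-gas and fingertip outcomes. If inspired oxygen is not noted when the reading is taken, it cannot be reliably reconstructed later, so the gap has to be closed prospectively.

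**Working it through.** The section states no figure to reproduce. The only related figure is the sample size: 66 in a 1:1:1 ratio gives 66/3 = 22 per arm, and 66/0.95 = 69.5, rounded up to 70, matches the stated total after 5% dropout. The article gives no effect size, SD or oxygen-use rate for PaO2 or SaO2, so everything below is an illustration with assumed inputs.

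**Ranking of two patients.** PaO2 = (PaO2/FiO2) × FiO2.
- Sicker patient on oxygen: 250 × 0.40 = 100 mmHg.
- Healthier patient on room air: 380 × 0.21 = 79.8, about 80 mmHg.

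Raw PaO2 puts the sicker patient about 20 mmHg higher.

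**Effect on the comparison.** Assumed: room-air PaO2 mean 70 mmHg in controls and 80 in LIPUS (true gain 10), SD 12, 22 per arm, two-sample t test, two-sided alpha 0.05. Patients whose room-air PaO2 lies below a threshold receive oxygen, which raises PaO2 by 15 or 25 mmHg on average (SD 5).

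Share on oxygen = Φ((threshold − mean)/12). Expected raw difference = 10 − rise × (control share − LIPUS share). For example, at threshold 65 the shares are Φ(−5/12) = 0.338 and Φ(−15/12) = 0.106; with a rise of 25 the difference is 10 − 25 × 0.232 = 4.2 mmHg. The differences and powers below come from 20,000 simulated trials per scenario, which agree with this formula.

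| Threshold (mmHg) | Rise (mmHg) | On oxygen, control / LIPUS | Raw difference (mmHg) | Power |
|---|---|---|---|---|
| none on oxygen | – | 0 / 0 | 10.0 | 0.77 |
| 55 | 15 | 10% / 2% | 8.7 | 0.74 |
| 60 | 15 | 20% / 5% | 7.7 | 0.70 |
| 60 | 25 | 20% / 5% | 6.1 | 0.52 |
| 65 | 15 | 34% / 11% | 6.5 | 0.62 |
| 65 | 25 | 34% / 11% | 4.2 | 0.31 |

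**Other assumed gains.** With a true gain of 8 mmHg, power is 0.58 with nobody on oxygen and 0.54 to 0.19 across the same scenarios. With a gain of 12 it is 0.90, and then 0.88 to 0.48.

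**No true effect.** The rejection rate stays between 0.046 and 0.052 in all scenarios.

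**Oxygen unrelated to need.** If 30% of each arm receive oxygen whatever their state, the mean difference is unbiased at 10 mmHg, but the added spread lowers power to 0.65 (rise 15) or 0.50 (rise 25).

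**The case against.** The strongest reply is that this is an unstated measurement condition. Inspired oxygen is a setting and not an analyser output, so its absence from a list of analyser outputs does not prove that nobody records it. A journal article may leave the sampling condition to the full protocol or case report form. That is fair as to what is recorded at the bedside. It does not settle what is compared: the article fixes the outcome variables, and all the oxygenation variables are raw values. It also states measurement conditions for other outcomes, such as sitting position for ultrasound, fasting morning blood, and auscultation without expectoration aids.

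The second reply is that oxygen use may be rare. The background section calls most viral infections mild to moderate, participants must be able to cooperate with examinations that include lung function tests, and the remarks on impaired oxygenation describe the disease in general. This stands as a limit on size. Some oxygen use remains plausible in inpatients with no severity limit and with suctioned patients foreseen, but its extent is unknown.

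Three stronger readings are tempting, and the article does not support them:
- A reader might infer that a LIPUS effect will be masked. Without an oxygen-use rate, effect size or SD, masking is possible and not established.
- A reader might infer that unequal oxygen use will produce a false difference. Under randomisation with the same need-driven practice in both arms, type I error stays near 0.05. A false difference would need oxygen practice to differ by arm for some other reason, which nothing in the article shows.
- A reader might infer that the secondary objective cannot be answered. It is worded as a difference in arterial oxygen saturation, and saturation is measured. The weakness is that raw saturation is a poor guide to gas exchange when some patients are on oxygen.

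**Conclusion.** The point holds as a weakness in the definition of secondary outcomes. Followed as written, the plan compares raw PaO2 and SaO2 between arms without regard to the oxygen breathed, and need-driven oxygen biases that comparison towards no difference. The loss runs from none, if nobody is on oxygen at the readings, to large: in the main illustration the 10 mmHg gain shrinks to between 8.7 and 4.2 mmHg, and power falls from 0.77 to between 0.74 and 0.31. These figures rest on an assumed mean, SD, gain, threshold and oxygen response, with up to 34% of controls on oxygen. The direction of the bias does not depend on the exact values, provided that oxygen follows need and LIPUS reduces that need. The primary CT outcome is untouched, so this should be corrected but does not threaten the main conclusion.

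**What to change.** In Blood gas analysis and fingertip SaO2 monitoring:
- Record the inspired oxygen at every blood gas and every fingertip reading: room air, or device with flow or FiO2.
- Make PaO2/FiO2 the blood-gas oxygenation outcome compared between arms, and keep raw PaO2 and SaO2 as descriptive values.
- Report oxygen use by arm alongside the fingertip readings.
- Treat a saturation/FiO2 ratio as supportive only. Near the saturation ceiling it mainly reflects the prescribed oxygen: at 97% it is 97/0.21 = 462 on room air and 97/0.40 = 243 on FiO2 0.40.

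The cost is one extra field at readings already scheduled and a short change to the outcome definition. A small downside is that FiO2 on nasal cannula has to be estimated from flow. No rule on oxygen treatment changes.
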